### Sample size

2.4

No clinical trial has been conducted to evaluate the efficacy of GJS compared with placebo on the SCORAD index for AD. Therefore, we determined a required sample size of 23 per group based on recommendations by a previous statistical study.^[17]^ Considering an assumed dropout rate of 20%, 58 participants, 29 in each group will be required.

### Recruitment

2.5

Recruitment began in September 2019 and is expected to end by October 2020. The study will be advertised through the bulletin boards at the hospital and local landmarks, the homepage of the hospital, the local newspaper, local online communities, and on public transportation. The posters will contain brief descriptions of the inclusion and exclusion criteria, the purpose of the study, and interventions used.

### Randomization and blinding

2.6

Participants will be randomly assigned to 1 of the 2 groups with a 1:1 ratio. An independent statistician will generate the blocked randomization using SAS software version 9.4 (SAS institute. Inc., Cary, NC) and pass it to the pharmaceutical company (Hanpoong Pharm & Foods Co., Ltd.). Experimental drugs will be allocated and labeled based on the randomization number by the pharmaceutical company. Accordingly, the hospital will be provided with GJS and the placebo sealed in opaque aluminum packages and labeled with the random numbers. The participants will be assigned a randomization number and the clinical trial pharmacist will provide the packaged drugs to the participants based on the randomization number. All researchers and participants will be blinded for the assignment process until the trial is completed unless a serious adverse event occurs. The generated numbers will be sealed in opaque envelopes and stored in double-locked cabinets.

### Intervention

2.7

Hanpoong Pharm & Foods Co., Ltd. manufactures the GJS and placebo in compliance with Korea Good Manufacturing Practice (KGMP) standards. Quality control and quality assurance for quality and safety testing, packaging, and contents of the treatment drug, including checks for potential contaminants such as heavy metals or steroids, will be undertaken by the manufacturers to ensure drug stability and quality.

GJS used in this study (Hangpoong *Gwakhyangjeonggi-san* extract granule) is dried, brown granules extracted with water. The extract is permitted and regulated by the MFDS and is composed of 13 herbs (Table 2). The placebo is made of lactose hydrate, corn starch, ginseng flavored powder, and caramel coloring. Both drugs will be identical in appearance, shape, taste, and color (brown).

**Table 2 T2:**
[figure not shown]
Composition of the *Gwakhyangjeonggi-san* (GJS).

GJS and placebo granules are sealed in opaque aluminum bags and administered to participants in doses of 3 g. The pharmacists will instruct the participants to dissolve GJS or placebo from each package in water and take the solutions 3 times per day 30 minutes before breakfast, lunch, and dinner or between meals for 8 weeks. All participants will be requested to return remains of drugs for calculating compliance.

Participants who have been receiving medication for chronic diseases such as hypertension and diabetes mellitus prior to the initiation of this study will be allowed to continue their regimen if it is a medication unlikely to affect the results. Care will be taken not to alter the dosage or type of drug during the study. Participants of both groups will be prohibited from the concomitant use of medication such as steroids, antihistamines, and immunosuppressive drugs that can potentially affect the outcome of this experiment until after the 8-week follow-up.

### Outcome measurement

2.8

#### Atopic dermatitis symptoms

2.8.1

Disease severity and quality of life will be assessed using SCORAD, the eczema area and severity index (EASI), the Dermatology Life Quality Index (DLQI), and EuroQoL 5 dimensions 5 levels (EQ-5D-5L), respectively. The primary outcome of the present study is the difference between the SCORAD of the 2 study groups before (week 0) and after (week 8) medication has been administered. SCORAD, EASI, DLQI, and EQ-5D-5L also will be assessed at week 0, 4, and 8.

#### Gastrointestinal symptoms

2.8.2

The Korean Gastrointestinal Symptom Rating Scale (KGSRS) and Nepean Dyspepsia Index-Korean version (NDI-K) will be assessed at weeks 0, 4, and 8.

#### Immune biomarker analysis

2.8.3

Total serum immunoglobulin E (IgE) and eosinophil cationic protein (ECP) will be evaluated at weeks 0 and 8.

The specific IgE levels for the following 12 specific antigens will be measured using the ImmunoCAP assay at weeks 0, and 8: egg white, milk, walnut, wheat, peanut, soy, shrimp, buckwheat, fish (cod), meat mixture, *Dermatophagoides pteronyssinus*, and *Dermatophagoides farina*. A blood sample will be obtained for further analysis of the immune biomarkers and metabolites.

#### Microbiome analysis

2.8.4

Microbiome analysis will be conducted from fecal samples. The deoxyribonucleic acid (DNA) in the collected fecal samples are isolated using the FastDNA SPIN kit (MPBio). Polymerase chain reaction (PCR) will be performed using a primer to amplify the V3–V4 gene region of 16S ribosomal ribonucleic acid (rRNA) from the separated DNA. After purification of the amplified product, a genomic DNA library will be constructed and the nucleotide sequence analyzed. Fecal sample collection for microbiome analysis will be performed at week 0 and 8.

#### Safety outcomes

2.8.5

For the safety of the study participants, complete blood cell counts, liver function tests, lipid tests, and urine analyses will be performed at the screening phase and end of the trial. Vital signs will be examined at every visit. For female participants, urine human chorionic gonadotropin (hCG) will be checked at the screening visit to test for pregnancy. The investigator will ask about any expected or unexpected adverse events and record details of adverse events in the case report form (CRF). When serious adverse events occur, the investigator will immediately report this to the institutional review board (IRB) within 24 hours. If a serious adverse event occurs, the investigators will determine whether it is acceptable, whether the experimental drug should be continued or stopped, and whether the trial should be amended or ended.

### Data and safety monitoring

2.9

To protect the rights and welfare of the participants and to control the quality of the study, monitoring will be performed. According to the planned protocol and standard operating procedures, a clinical research associate (CRA) will monitor if the trials are proceeding according to the protocol by performing a cross-check of the informed consent form, CRF, original chart of the participants, and drug management records. The trial data will be saved in an electronic data capture system (Medidata Rave; Medidata Solutions Inc., New York, NY). A clinical research coordinator will call patients during weeks 2 and 6 to promote participant retention and drug compliance. A separate storage location will be used to store the data and documents related to the clinical trial, and security will be maintained. After drafting the final report, a person in charge of the storage will be designated to keep the documents related to the clinical trial for 3 years from completion of the clinical trial. After completion of the study, the originals of the clinical trial CRF and other data collected and acquired during the study will be stored separately in accordance with the IRB regulations.

### Statistical analysis

2.10

The measured variables, including the primary and secondary outcomes, will be assessed using the full analysis set based on the intention-to-treat principles. The per-protocol analysis set will be used for the sensitivity analysis. The baseline characteristic values in both groups will be expressed as a mean and standard deviation for continuous variables that are normally distributed or medians and interquartile ranges for non-normal data. Frequencies and percentages will be used to present categorical variables. Baseline differences between groups will be assessed using an independent 2-sample *t* test or Wilcoxon rank-sum test for continuous variables. The Chi-square test or Fisher exact test will be used for categorical variables. A mixed-effect model repeated measure (MMRM), which sets participants as a random factor and the group and visit as fixed factors, will be performed to analyze the between-group differences in the primary and secondary outcome measures. The Student paired *t* test and repeated-measures analysis of variance (ANOVA) will be used to evaluate the intra-group time changes in continuous values. Chi-square or Fisher exact tests will be used to evaluate the intra-group time changes in categorical values. MMRM does not require the replacement of missing data, and the missing data in the intra-group analysis will be replaced using the last observation carried forward method. The level of significance will be set at 0.05 (2-tailed). All analyses will be performed by an independent statistician using SAS version 9.4 (SAS Institute Inc., Cary, NC).

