**Methods and analysis::**

A randomized, double-blind, placebo-controlled, parallel-group, clinical trial has been designed to investigate the clinical efficacy and safety of GJS on patients with AD that have gastrointestinal symptoms. A total of 58 participants with AD will be recruited and randomly allocated to the GJS or placebo group in a 1:1 ratio. The participants will be administered GJS or placebo granules 3 times a day for 8 weeks. Data will be collected from the participants at baseline and after 4 and 8 weeks. The primary outcome measure will be the mean change in the SCORing of Atopic Dermatitis (SCORAD) index from baseline to 8 weeks. The secondary outcomes will include the eczema area and severity index (EASI), dermatology life quality index (DLQI), EuroQoL 5 dimensions 5 levels (EQ-5D-5L), and immunological factors. The Korean Gastrointestinal Symptom Rating Scale (KGSRS), Nepean Dyspepsia Index will also be obtained for assessing the gastrointestinal status.

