### Study design

2.2

This randomized, double-blind (patient, practitioner, and assessor), placebo-controlled, parallel-group, clinical trial will be conducted at the Kyung Hee University Korean Medicine Hospital at Gangdong (Seoul, Republic of Korea). A total of 58 participants will be recruited for this trial and participants will be assigned either GJS treatment group or placebo controlled group. The trial will consist of an 8-week oral administration of GJS with 2 visits at 4-week intervals. Before enrollment, all participants will undergo a 7-day run-in period. The enrolled participants will be randomly allocated to 2 parallel groups: the GJS group and the placebo group. The study design flow chart is shown in Fig. 1 and Table 1. This protocol is based on the Standard Protocol Items: Recommendations for Interventional Trials.

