#### Inclusion criteria

2.3.1

Participants will be considered eligible for inclusion if they meet the following criteria:

1.Men or women aged 19 to 60 years.2.Diagnosis of AD based on the Hanifin and Rajka diagnostic criteria, which require that ≥3 major features and ≥3 minor features be fulfilled.3.Diagnosis of gastroduodenal or bowel disorder based on the ROME IV Questionnaire.4.Moderate AD diagnosed by the SCORing of Atopic Dermatitis (SCORAD) index (score 25–50).5.Ability to comprehend the purpose of the study, the study procedure, and the properties of the investigational drug, as well as voluntary agreement to participate in the study (provision of written informed consent).

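### A participant random factor as the only stated within-participant structure implies compound symmetry, which is doubtful for SCORAD at weeks 0, 4 and 8 and may misstate the standard error of the week 0-8 contrast in either direction

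*Protocol article*

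**What the plan says.** Section 2.10 (Statistical analysis) sets out the between-group model for primary and secondary outcomes in one clause: "A mixed-effect model repeated measure (MMRM), which sets participants as a random factor", with group and visit fixed. It names no residual covariance structure and does not say whether week 0 is a response or a covariate. The test is two-sided at 0.05.

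The abstract gives the primary outcome as the "mean change in the SCORing of Atopic Dermatitis (SCORAD) index from baseline to 8 weeks". Section 2.8.1 sets the measurement times: "SCORAD, EASI, DLQI, and EQ-5D-5L also will be assessed at week 0, 4, and 8".

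Two other places bear on the variance at week 0. Section 2.3.1 restricts entry by severity: "Moderate AD diagnosed by the SCORing of Atopic Dermatitis (SCORAD) index (score 25–50". Section 2.2 adds: "Before enrollment, all participants will undergo a 7-day run-in period". Section 2.4 plans for 23 evaluable participants per group. No SD of SCORAD and no between-visit correlation is stated anywhere.

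**The concern.** A random participant effect with independent residuals gives every visit the same variance and every pair of visits the same correlation. There are two reasons to doubt that here.

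- **Correlation over time.** The introduction describes atopic dermatitis as relapsing. Scores at weeks 0 and 8 are plausibly less alike than scores at adjacent visits.
- **Variance over time.** Entry is limited to a 25-point band of SCORAD, while later scores are not limited. If week 0 is one of the responses, its variance may be smaller than that at weeks 4 and 8.

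Under compound symmetry the model does not estimate the variance of the week 0-8 change from that change alone. It uses the average over the three pairs of visits. If the week 0-8 change varies more than that average, the standard error is too small and the test rejects too often. If it varies less, the test is conservative. The primary outcome rests on this contrast.

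**Working it through.** **The plan's own figure.** 23 / (1 − 0.20) = 28.75, rounded up to 29 per group, 58 in total. This agrees with section 2.4. The 23 itself cannot be rebuilt, because no effect size, SD or power is given. I use n = 23 per arm with complete data; the 20% dropout is not simulated.

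**Inputs.** Visits at weeks 0, 4 and 8, two-sided 0.05 and n = 23 come from the article. All SDs and correlations below are assumptions, shown as a range. The calculations use group-by-visit means, because a week-8 contrast needs them. Section 2.10 does not list that interaction, which is a separate matter.

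**Formulas.** For visits i and j, the change variance is V(i,j) = SDi² + SDj² − 2·r(i,j)·SDi·SDj.
- True SE of the group contrast in week 0-8 change: √(2·V(0,8)/n).
- SE under compound symmetry (CS), in expectation: √(2·V̄/n), where V̄ is the mean of V(0,4), V(0,8) and V(4,8).
- SE ratio R = √(V̄/V(0,8)).
- Large-sample type I error ≈ 2Φ(−1.96·R).

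**Worked example.** SDs 7, 10, 12; r(0,4) = 0.6, r(0,8) = 0.4, r(4,8) = 0.7.
- V(0,4) = 49 + 100 − 84 = 65.0
- V(0,8) = 49 + 144 − 67.2 = 125.8
- V(4,8) = 100 + 144 − 168 = 76.0
- V̄ = 266.8/3 = 88.9, so the variance ratio is 88.9/125.8 = 0.707 and R = 0.841
- SE: √(2 × 88.9/23) = 2.78 under CS, against a true √(2 × 125.8/23) = 3.31
- Type I error ≈ 2Φ(−1.65) = 9.9%; simulation gives 9.6%, against 4.9% for the unstructured analysis

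**Range, week 0 as a response** (20,000 simulated trials per row, no true effect; with complete data the unstructured analysis equals a t test on the change):

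| SDs at weeks 0/4/8 | r(0,4) / r(0,8) / r(4,8) | Variance ratio CS/true | Type I error, CS |
|---|---|---|---|
| 7/10/13 | 0.6 / 0.4 / 0.7 | 0.68 | 10.3% |
| 6/8/9 | 0.6 / 0.4 / 0.7 | 0.72 | 9.2% |
| all equal | 0.7 / 0.5 / 0.7 | 0.73 | 9.4% |
| 7/10/10 | 0.6 / 0.5 / 0.7 | 0.86 | 6.5% |
| 7/10/10 | all 0.6 | 70/65 = 1.08 | 4.0% |
| 7/9/7 | all 0.5 | 61/49 = 1.24 | 2.9% |

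The unstructured analysis stays near 5% throughout. The third row shows that decaying correlation alone is enough to inflate the error. The last two rows show that unequal variances with constant correlation need not inflate it. Spread that rises through to week 8 with constant correlation inflates it only mildly: SDs 7/10/12 with all correlations 0.5 give V = 79, 109, 124, so R = √(104/109) = 0.977 and about 5.6%.

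**Entry window in isolation.** A latent normal score with SD 10 to 18, truncated to 25-50 at week 0, gives a week-0 SD of about 6.5 to 7.0 and a week-8 SD of about 8.5 to 14.5.
- Constant latent correlation 0.7: R = 1.01 to 1.02 for the week 0-8 change, type I error about 4.5-4.7%.
- Decaying latent correlation (0.8 at 4 weeks, 0.64 at 8): R = 0.85 to 0.86, type I error about 9-9.5%.

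The raw week-8 group difference behaves differently: with the window alone its SE ratio is 0.87 to 0.93 and its error about 7-9%. That is not the change named as primary.

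**Only weeks 4 and 8 as responses, week 0 as covariate.** The residual variance at week j is SDj²·(1 − r(0,j)²). In the worked example, week 4 gives 100 × 0.64 = 64.0 and week 8 gives 144 × 0.84 = 121.0. The mean is 92.5, the variance ratio 0.765, R = 0.874 and the error about 8.7%. In the truncation scenarios R is 1.00 with constant correlation and about 0.90 with decay. The effect is therefore generally smaller, though not in every scenario: SDs 7/10/12 with all correlations 0.5 give R = √(91.5/108) = 0.92.

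**The case against.** The strongest reply has four parts.

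- **The entry window does not do the damage.** A reader might infer that truncating SCORAD at entry is enough to make the week-8 error bars too narrow. The documents do not support that. With the window alone and constant correlation, the SE of the week 0-8 change is correct or slightly too wide. The article also does not tie the 25-50 band to the week-0 score: if it is applied before the 7-day run-in, week-0 values are less sharply truncated. This objection stands.
- **The inflated figures rest on inputs the article does not give.** This also stands. Decaying correlation is a reasonable expectation in a relapsing disease, but it remains an assumption, and other plausible values make the test conservative.
- **The effect listed in the model is not harmed.** With group and visit as the only fixed factors, the group effect is an average over visits, and compound symmetry does not distort its error. That is correct, but the primary outcome is the week 0-8 change, so the week-8 contrast is what the trial needs.
- **Covariance structure is analysis-plan detail.** The MMRM label leaves room for a residual structure set in a plan that is not shown, so the article does not strictly rule one out. But it does more than stay silent: it says how repeats are handled, and the only structure it names is the participant factor. A programmer following that clause would fit a random intercept.

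**Conclusion.** The point holds as a doubtful stated choice with an uncertain direction of error. Read literally, section 2.10 specifies compound symmetry, and that structure may misstate the standard error of the primary week 0-8 contrast. Under the assumed SDs and correlations, with 23 per arm, complete data and group-by-visit means, type I error runs from about 3% to 10%, against about 5% for an unstructured covariance. It rises clearly above 5% when correlation falls with time, and less so when only the spread keeps rising to week 8. It is at or below 5% when the window acts alone with constant correlation. The effect is generally smaller when only post-baseline visits are responses, and absent for the averaged group effect.

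A claim that type I error will exceed 5%, or that the confidence intervals will be too short, goes further than the documents allow, since they give no SD or correlation. The case for change does not need that claim: the unstructured model holds its level across these scenarios and the described one does not.

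**What to change.** Replace the participant random factor with an unstructured within-participant covariance (in SAS, REPEATED visit / SUBJECT=participant TYPE=UN) and Kenward-Roger degrees of freedom. Name a fallback for non-convergence, such as heterogeneous Toeplitz, then compound symmetry with robust standard errors. State whether week 0 is a response or a covariate, and read the primary result from the week-8 contrast: the group difference in week 0-8 change. That contrast requires a group-by-visit term in the model.

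The cost is about one line of model specification. Three visits need 6 covariance parameters (3 if only weeks 4 and 8 are responses) in place of 2, which is feasible with 58 participants. Intervals may come out slightly wider.

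### As listed, the MMRM has no group-by-visit term or week-8 contrast, so its group effect averages over visits and does not estimate the primary week 0 to week 8 SCORAD change

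*Protocol article*

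**What the plan says.** **Endpoint.** The abstract (Methods and analysis) defines the primary outcome as the "mean change in the SCORing of Atopic Dermatitis (SCORAD) index from baseline to 8 weeks". Section 2.8.1 gives it as "the difference between the SCORAD of the 2 study groups before (week 0) and after (week 8) medication has been administered". Both fix week 8 as the time point and change from week 0 as the quantity.

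**Visits.** Section 2.8.1 also says that "SCORAD, EASI, DLQI, and EQ-5D-5L also will be assessed at week 0, 4, and 8". Section 2.8.3 has total IgE and ECP measured at weeks 0 and 8 only.

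**Model.** Section 2.10 specifies an MMRM "which sets participants as a random factor and the group and visit as fixed factors, will be performed to analyze the between-group differences". It applies to primary and secondary outcomes alike. The sentence names participant, group and visit. It names no group-by-visit interaction, no baseline covariate and no contrast at a particular visit, and does not say whether the response is the score or its change.

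**Other tests in section 2.10.** The two-sample *t* and Wilcoxon tests are for baseline differences. The paired *t* test and repeated-measures ANOVA are for change within a group. The MMRM is therefore the only stated between-group analysis of the primary outcome.

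**The concern.** A model with group and visit as its only fixed terms assumes that the group difference is the same at every visit. It returns one group effect, pooled over whichever visits are in the response, and so has no term specific to week 8.

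If the raw score is the response, week 0 is one of the pooled visits. The group difference there is zero in expectation under randomisation, so it pulls the pooled effect towards zero. The term that would carry a treatment effect on change is then the interaction, which is not listed.

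If change is the response, week 4 has the same weight as week 8, although the endpoint is week 8 alone.

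What is at stake is which number becomes the primary result. A programmer coding the sentence as it stands would report an estimate and p-value for a quantity that sections 2.8.1 and 2.10 do not jointly define. That estimate would usually be closer to zero than the week-8 effect, in a trial planned for 23 evaluable participants per arm.

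**Working it through.** **Inputs from the protocol article.** Section 2.4: "we determined a required sample size of 23 per group based on recommendations by a previous statistical study", with 20% dropout and 58 in total. Section 2.10: two-sided 0.05. Section 2.8.1: SCORAD at weeks 0, 4 and 8.

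**The plan's own figure.** 23 / (1 − 0.20) = 28.75, rounded up to 29 per group, or 58 in total. This reproduces. The 23 itself cannot be derived, because no effect size, SD or power is given.

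**What the group term estimates.** Let d0, d4 and d8 be the group differences in mean score at weeks 0, 4 and 8, with d0 = 0 in expectation. With complete data and a random participant intercept, the group coefficient is the simple average over the visits in the response:

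- raw score at weeks 0, 4, 8: (d0 + d4 + d8) / 3
- change at weeks 4, 8: (d4 + d8) / 2
- target: d8 − d0 = D

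| Week-4 effect | Raw version | Change version |
|---|---|---|
| 0 | 0.33 D | 0.50 D |
| D/2 | 0.50 D | 0.75 D |
| D | 0.67 D | 1.00 D |

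For IgE and ECP the raw version gives (0 + D)/2 = 0.50 D. The change version has a single post-baseline value and gives D, which is correct.

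**Illustrative power.** Assumptions not in the documents: 23 per arm, complete data, D set at 0.845 SD of the week-8 change (80% power for a two-sample *t* test), SDs at weeks 0, 4, 8 from (7, 7, 7) to (7, 10, 13), correlations 0.4–0.7, and half the effect present at week 4.

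One case in full, with all SDs 7 and correlation 0.5:

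- Week-8 change: SD = 7 × √(2 × 0.5) = 7.00, so D = 0.845 × 7.00 = 5.92.
- Raw version: SD of the three-visit mean = 7 × √((1 + 2 × 0.5)/3) = 5.72. Effect = 0.50 × 5.92 = 2.96. Noncentrality = (2.96/5.72) × √(23/2) = 1.75. Power is about 40%.
- Change version: SD = 7 × √(1.5 × 0.5) = 6.06. Effect = 0.75 × 5.92 = 4.44. Noncentrality = (4.44/6.06) × √(23/2) = 2.48. Power is about 68%.

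The same formulas at the corners of the assumed range, with one correlation common to all visit pairs:

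| SDs | Correlation | Raw version | Change version |
|---|---|---|---|
| 7, 7, 7 | 0.4 | 51% | 68% |
| 7, 7, 7 | 0.7 | 23% | 68% |
| 7, 10, 13 | 0.4 | 58% | 82% |
| 7, 10, 13 | 0.7 | 32% | 82% |

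A lower correlation between weeks 0 and 8 than between adjacent visits moves the top of the last column to about 83%. The ranges are therefore about 23–58% (raw) and 68–83% (change), against 80% for the direct week-8 comparison.

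**Full effect by week 4.** In the worked case the change version has effect 5.92 and SD 6.06. Noncentrality is (5.92/6.06) × √(23/2) = 3.31 and power about 90%. Here averaging helps, and the estimate equals D.

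**Check by model fitting.** In 200 simulated trials (correlation 0.5, half the effect at week 4), mixed models with only group and visit gave 0.51 D (raw) and 0.73 D (change). With group-by-visit added, the week-8 versus week-0 contrast gave 0.96 D with power 78%.

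**The case against.** The strongest reply is that the sentence in section 2.10 sorts factors into random and fixed and does not write out a model. It does not expressly exclude an interaction. Analyses called MMRM commonly include treatment-by-visit and a contrast at the endpoint visit, and an article condenses a fuller protocol. Nor does the article say that the group main effect is the primary test. This stands to the extent that the full protocol or SAP may already have the right model. It does not remove the point: the article lists the model's terms, and the list does not yield the endpoint it states elsewhere. That is more than a detail left for later.

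Three further objections are right and limit the claim.

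- The abstract's wording points towards change as the response. On that reading the dilution is milder, disappears if the effect is full and constant from week 4, and does not arise for IgE and ECP.
- Every power figure rests on assumed SDs, correlations and time course.
- If the treatment has no effect at any visit, the averaged group term is also null.

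A reader might infer that the plan forbids an interaction, that the trial will lose a known amount of power, that IgE and ECP effects will be halved in any case, or that the false-positive rate is inflated. The documents support none of these. The first is not stated, the second needs inputs that the article does not give, the third holds only for a raw-score response, and the fourth does not follow from averaging over visits.

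**Conclusion.** The mismatch holds. Fitted with the terms listed in section 2.10, the group effect is a visit average. It equals the stated primary endpoint only when the response is change from baseline and the effect is the same at weeks 4 and 8. This follows from the listed terms and the visit schedule and needs no assumed SD or correlation.

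The size is conditional. The dilution depends on how much of the effect is present at week 4 and on the choice of response, and ranges from one-third of the week-8 effect to none. The power ranges above show that the consequence can matter with 23 per arm. They are illustrations and not forecasts for this trial.

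It should be settled before unblinding, because it decides which estimate is the primary result.

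**What to change.** Amend the model sentence in section 2.10 to do three things:

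1. Add the group-by-visit interaction to the fixed effects.
2. State how baseline SCORAD enters: either as a covariate with change at weeks 4 and 8 as the response, or with week 0 kept in the response.
3. Name the between-group contrast in change from baseline at week 8, with its 95% CI, as the single primary test.

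Use the same form for secondary outcomes with repeated visits. For IgE and ECP, make clear that the target is the group difference in change at week 8.

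If the full protocol or SAP already specifies this, confirm it and correct the published sentence to match.

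The cost is a sentence or two before unblinding, with no extra data and no change to the planned 58 participants. The downside is some loss of power if the effect is already full and constant from week 4: 80% against about 90% for the averaged change in the worked case.

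### The between-group MMRM lists no baseline SCORAD covariate although every participant has one, which costs precision and leaves error conditional on chance imbalance

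*Protocol article*

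**What the plan says.** Section 2.10 (Statistical analysis) gives one model for the between-group comparison: an MMRM with participant as the random term and "the group and visit as fixed factors", used "to analyze the between-group differences in the primary and secondary outcome measures". No covariate appears in that sentence, and no other section mentions adjustment for baseline.

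Baseline SCORAD is available for everyone. Section 2.3.1 requires a score of 25 to 50 at entry, and section 2.8.1 states that "SCORAD, EASI, DLQI, and EQ-5D-5L also will be assessed at week 0, 4, and 8".

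The abstract defines the primary outcome as "the mean change in the SCORing of Atopic Dermatitis (SCORAD) index from baseline to 8 weeks". Section 2.8.1 describes it as a difference between the groups in SCORAD before and after medication. Section 2.10 does not say whether the modelled response is the change or the raw score, or whether week 0 counts as one of the visits.

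Separately, section 2.10 plans significance tests of baseline comparability: "Baseline differences between groups will be assessed using an independent 2-sample" t test or a rank-sum test, with Chi-square or Fisher tests for categorical variables.

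**The concern.** In a trial planned on 23 evaluable participants per arm, the baseline value of the outcome is usually the most useful covariate. The model as listed does not estimate its relation to the week-8 score. Two things are at stake. The first is precision: part of the variation in the outcome that baseline could explain stays in the error term. The second is conditional error: once the arms happen to differ at baseline, the estimated effect is displaced by an amount that an adjusted analysis would remove.

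The direction of that displacement depends on the response, which section 2.10 leaves open. With a change score, the arm that starts higher tends to fall further through regression to the mean, so the imbalance is over-corrected. With a raw week-8 score, the arm that starts higher tends to end higher, and nothing corrects it.

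**Working it through.** **The plan's own figure.** Section 2.4 takes 23 per group and 20% dropout: 23 / 0.8 = 28.75, rounded up to 29 per group, 58 in total. This reproduces. The 23 itself cannot be checked, because no effect size, SD or power is given. With a two-sided 0.05 t test, 23 per arm has 80% power for a standardised difference of about 0.84, so precision matters.

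**Assumptions.** The article gives no SCORAD SDs and no baseline to week-8 correlation. Write s0 and s8 for the SDs at weeks 0 and 8, and r for their correlation. Three assumed sets:
- A: s0 = s8, r = 0.5 (shown with 7 and 7)
- B: s0 = 7, s8 = 9, r = 0.45
- C: s0 = 7, s8 = 12, r = 0.4

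**Precision.** Per participant, the change-score variance is s8² + s0² − 2·r·s0·s8, and the baseline-adjusted variance is s8²(1 − r²).
- A: 36.75 / 49.0 = 0.75
- B: 64.6 / 73.3 = 0.88
- C: 120.96 / 125.8 = 0.96

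Against a raw week-8 score the ratio is 1 − r²: 0.75, 0.80 and 0.84.

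**Power.** Fix the effect so that the change-score t test has 80% power at 23 per arm (noncentrality 2.865 on 44 df). Divide the noncentrality by the square root of the variance ratio, use 43 df, and inflate the adjusted variance by 1 + 1/42 for estimating the slope. Power becomes:
- A: 89%
- B: 84%
- C: 81%

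**Size of a chance imbalance.** If entry scores were spread uniformly over 25 to 50, the SD would be 25/√12 = 7.2. With 29 per arm, the 95% range of the baseline difference is ±1.96 × 7.2 × √(2/29) = ±3.7 points.

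**Effect on the estimate.** That 3.7 is a difference at baseline, not the error in the treatment effect. With b = r·s8/s0 as the regression slope of week 8 on baseline, an imbalance D moves the change-score effect by (1 − b)·D in one direction and the raw-score effect by b·D in the other. For D = 3.7:

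| Set | b | Change score | Raw week 8 |
|---|---|---|---|
| A | 0.50 | 1.9 | 1.9 |
| B | 0.58 | 1.6 | 2.1 |
| C | 0.69 | 1.2 | 2.5 |

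**If week 0 is itself a response visit.** With only main effects of group and visit, the group term averages in a visit that has no treatment effect. With equal weights, it recovers (0 + 0.5 + 1)/3 = 50% of the week-8 effect if week 4 shows half of that effect, and (0 + 1 + 1)/3 = 67% if week 4 shows all of it. This reading does not adjust for baseline either, and it is a further reason to state the response.

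**The case against.** The strongest reply is that one sentence in a journal article is not a full model specification. It also omits the response and the covariance structure, it speaks of factors rather than covariates, and a longer protocol exists (version 1.4, section 2.11). This stands in part: the full protocol or analysis plan may already include baseline. But the article does name the model's terms and leaves baseline out, and an analysis plan that followed those terms would inherit the omission.

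Three stronger readings are tempting, and the document does not support them.
- *The effect estimate is biased, or type I error is inflated.* Neither follows. Under 1:1 randomisation the unadjusted comparison is unbiased over allocations, and its standard error already reflects chance imbalance. The absence of stated stratification by severity does not change this.
- *Baseline is ignored and imbalance is left wholly uncorrected.* That is true only of a raw post-baseline response. The abstract's outcome is a change from baseline, which uses every baseline score, though with a fixed slope of 1.
- *Significance tests at baseline take the place of adjustment.* Section 2.10 does not say that they select covariates or alter the efficacy analysis. After randomisation they test a hypothesis already known to be true, but they affect no efficacy estimate.

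It is also fair to say that the gain rests on assumed values and nearly vanishes in set C.

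**Conclusion.** The point holds as one of efficiency and conditional error. None of the readings of the listed terms set out above estimates the baseline slope, and the data needed to do so are collected on everyone. Over the assumed sets, the gain against a change score runs from almost nothing (80% to about 81%) to worthwhile (80% to about 89%). The error from an imbalance at the edge of its 95% range is about 1.2 to 1.9 SCORAD points. These sizes depend on the assumed SDs and correlations and on a uniform spread of entry scores. The imbalance figure uses 29 randomised per arm, and the power figures use 23 evaluable. The change is worth making because it costs almost nothing, not because the present analysis is invalid.

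**What to change.** Before unblinding, so that the choice of covariate cannot depend on the results:
- State the response: post-baseline SCORAD at weeks 4 and 8, or its change from week 0.
- Fit the MMRM with group, visit, group-by-visit, baseline SCORAD and baseline-by-visit, and name the week-8 group contrast as primary. An equivalent constrained longitudinal model, with week 0 as a response and a common baseline mean, would also do.
- Use the same form for EASI, DLQI, EQ-5D-5L, KGSRS and NDI-K, each with its own baseline.

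The cost is a wording change and one or two degrees of freedom; no new data are needed. If the full protocol or analysis plan already specifies this, it is enough to confirm it and align the two texts. Dropping the baseline p-values and reporting baseline descriptively is an optional reporting change that alters no efficacy result.
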